## Methods/design

### Trial design

This will be a single-center, single-blind, parallel-group, randomized controlled trial. Using a 2-by-2 factorial design, high-risk adult patients undergoing elective cardiac surgery will be randomly assigned to receive either a best PEEP (calculated with a PEEP test) ventilation or a zero PEEP strategy before and after CPB and CPAP (equal to the best PEEP) or no ventilation (patient disconnected from the circuit) during CPB.

We will recruit all patients that will match the eligibility criteria at the preoperative evaluation. The protocol structure was written in according to the Consolidated Standards of Reporting Trials (CONSORT) 2010 Statement [14] and follows the Standard Protocol Items: Recommendations for Interventional Trials (SPIRIT) Statement [15]. The SPIRIT Figure of this trial is illustrated in Fig. 1. The SPIRIT Checklist of this trial can be found in Additional file 1. Patients will also be evaluated in terms of (1) shunt fraction and (2) data of respiratory mechanics, such as static compliance, flow, and additional resistance. All these parameters will be determined: (1) immediately after anesthesia induction, (2) before CPB, (3) during CPB, (4) off pump, and (5) end of surgery.

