#### Lung mechanics determination [19]

Quasi-static compliance of the respiratory system (Cqst,rs) will be calculated as:$$ \mathrm{Tidal}\ \mathrm{volume}/\left(\mathrm{End}\ \mathrm{inspiratory}\ \mathrm{plateau}\ \mathrm{pressure}- PEEPtot\ \left(\mathrm{ml}/{\mathrm{cmH}}_2\mathrm{O}\right)\right), $$

where *PEEPtot* is the end-expiratory pressure at period of no flow. Measurement will be performed with an inspiratory pause of 60%.

Dynamic compliance of respiratory system (Cqdyn,rs), induced by thorax opening, will be calculated as:

$$ \mathrm{Tidal}\ \mathrm{volume}/\left(\mathrm{End}\ \mathrm{inspiratory}\ \mathrm{peak}\ \mathrm{pressure}- PEEPtot\ \left(\mathrm{ml}/{\mathrm{cmH}}_2\mathrm{O}\right)\right) $$

Measurement will be performed with an inspiratory pause of 10%.

Airway resistance (Rmin,rs) will be calculated as:$$ \left( Ppeak-{P}_1\right)/{V}^{'}, $$

where *Ppeak* is the peak inspiratory pressure, *P*_1_ is the airways’ pressure at the point of zero flow and *V*′ is the inspiratory flow. Measurement will be performed with an inspiratory pause of 60%. Lung mechanics will be determinate immediately after every PEEP test execution.

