#### Shunt fraction calculation

Shunt fraction will be determined before surgery and after surgery in the operating room during general anesthesia, before patient discharge from operating room. Shunt fraction will be assessed as follows in all patients:$$ Qs/ Qt=\left({PAO}_2-{PaO}_2\right)\times 0.0031/C\left(a- vmixed\right){O}_2+\left[\left({PAO}_2-{PaO}_2\right)\times 0.0031\right], $$

where:*PAO*_*2*_ is oxygen alveolar concentration*PaO*_*2*_ is oxygen arterial concentration*C(a-vmixed)O*_*2*_ is arteriovenous difference in oxygen concentration0.0031 is a conversion factor to volume percent for O_2_

Measure will be performed while breathing 100% oxygen for 20 min, to achieve a complete hemoglobin saturation.

If a PAC is placed, according to clinical indications, the shunt fraction will be calculated from the following formula:$$ Qs/ Qt={ CcO 2}_{-}\ {CaO}_2/{CcO}_2- Cv(mixed){O}_2\times 100, $$

where:*CcO*_*2*_ is pulmonary capillary blood O_2_ content, estimated with the following equation:

$$ {CcO}_2=\left(\mathrm{Hb}\times 1.34\right)+\left(0.0031\times {PAO}_2\right), $$
*CaO*_*2*_ is arterial oxygen content*Cv(mixed)O*_*2*_ is oxygen content in blood samples obtained from the pulmonary artery*PAO*_*2*_ is alveolar oxygen partial pressure

Blood samples will be collected from the arterial catheter and the pulmonary artery catheter, under a FiO_2_ of 100% in the same moment.

Furthermore, blood-gas analyses (BGA) will be performed on arterial blood:After anesthesia inductionAfter sternotomy, together with heparinizationBefore sternosynthesis, together with protamine administrationBefore discharge from the operating room

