### Statistical considerations

#### Sample size

Sample size calculation was based on a two-sided α error of 0.05 and a 80% power (β). On the basis of our experience, we anticipate that the 50% of patients with ventilation cessation during CPB and no PEEP before and after CPB will reach the composite endpoint of EFL after CPB and respiratory complications at 5 days, while only the 30% of the patients treated with an optimal ventilatory strategy will develop this composite endpoint. Including a drop-out fraction of 10%, we will enroll 51 patients per group, 204 in total.

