#### Data analysis

A statistical consultant dedicated, but not involved in patient management, will provide independent consultancy for data-quality checking and statistical analysis, and will be responsible for the statistical analysis. Data will be analyzed by means of SPSS 25.0 software. All data analyses will be carried out according to a pre-established intention-to-treat analysis plan. In addition, per-protocol analyses will be carried out, but only as a means to explore safety and feasibility. We will analyze patients in the treatment group to which they are allocated. Two-sided significance tests will be used. Dichotomous variables will be analyzed using the two-tailed ***χ***^2^ test, using the Yates’ correction when appropriate. Continuous variables will be compared by analysis of variance or the non-parametric Kruskal-Wallis test. Relative risks with 95% confidence intervals and differences between medians with 95% confidence intervals (using the Hodges-Lehmann estimation) will be calculated when appropriate.

The principal comparison will be between the patients who will or will not receive best PEEP ventilation and who will or will not receive CPAP during CPB.

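### Compliance, airway resistance and shunt are read repeatedly in each patient, but the only method stated for continuous variables names neither a baseline nor a within-patient term

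*Protocol article*

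**What the plan says.** **Analysis.** Under Data analysis, all continuous variables come under one sentence: "Continuous variables will be compared by analysis of variance or the non-parametric Kruskal-Wallis test". The same section adds Hodges-Lehmann differences between medians, which are unadjusted effect measures. It also refers to a pre-established analysis plan, which is not shown.

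**Measurements.** The schedule is given in several places:
- Trial design, on shunt and respiratory mechanics together: "All these parameters will be determined: (1) immediately after anesthesia induction, (2) before CPB". The list continues to five time-points.
- Lung mechanics determination: "Lung mechanics will be determinate immediately after every PEEP test execution". The EFL determination section lists six such tests.
- Table 4 marks compliance and airway resistance at five of its six rows, and shunt at two.
- Shunt fraction calculation: "Shunt fraction will be determined before surgery and after surgery in the operating room during general anesthesia". This agrees with Table 4 and not with Trial design.

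**Status.** Trial design introduces these as additional evaluations. The Endpoints section lists none of them as a primary or secondary endpoint.

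**The concern.** A first reading and one or more later readings on the same patient are usually correlated. An analysis that compares groups on a later value alone leaves the stable differences between patients in the error term. Adjusting for the first reading removes part of that variation at no cost in patients or measurements. Kruskal-Wallis compares independent groups on one value per patient. It cannot take a covariate, link readings over time or separate the two factors of the 2-by-2 design.

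The precision of the physiological comparisons is at stake, not their validity. With no model named, it is also open how the several stages are to be combined.

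A second matter decides whether adjustment is safe. A covariate must not itself be changed by the treatment whose effect is estimated. The Interventions section randomizes immediately before surgery and ties the PEEP setting to a test right after induction. The Lung mechanics section takes its readings right after each such test. Compliance is read at the PEEP then in use, and its formula subtracts total PEEP. The article does not say whether the first reading comes before or after the allocated PEEP is set.

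**Working it through.** **1. Patients per comparison.** The Sample size section gives 50% against 30%, two-sided alpha 0.05 and 80% power, and ends: "Including a drop-out fraction of 10%, we will enroll 51 patients per group, 204 in total". With the unpooled normal formula:
- n = (1.960 + 0.842)² × (0.50×0.50 + 0.30×0.70) / 0.20² = 7.85 × 0.46 / 0.04 = 90.3, so 91 per side.
- 91 / 0.90 = 101.1, so 102 per side and 204 in total.

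The stated figure is reproduced when each factor is compared across its margin (102 against 102). The pooled-variance formula gives 93, then 104 per side and 208 in total, within 3%. After 10% drop-out, 204 × 0.90 / 2 = 91.8, so about 92 evaluable patients per side.

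**2. Gain from the first reading.** The article gives no standard deviation and no within-patient correlation r, so r is an assumption shown over a range. Adjustment multiplies the residual variance by 1 − r² and the interval width by √(1 − r²). The equivalent number of patients per side is 92 / (1 − r²).

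| r | 1 − r² | √(1 − r²) | Interval narrower by | Equivalent patients per side |
|---|---|---|---|---|
| 0 | 1.00 | 1.000 | 0% | 92 |
| 0.3 | 0.91 | 0.954 | 5% | 101 |
| 0.5 | 0.75 | 0.866 | 13% | 123 |
| 0.7 | 0.51 | 0.714 | 29% | 180 |

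**3. The same gain as power.** For an illustrative difference of 0.4 SD at one stage (also an assumption), power = Φ(0.4 / √(2(1 − r²)/92) − 1.96):
- r = 0: Φ(0.753) = 77%
- r = 0.3: 81%
- r = 0.5: 88%
- r = 0.7: 97%

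**4. Is the first reading a valid baseline?**
- *CPAP factor.* CPAP is applied only during CPB. The first mechanics reading (Table 4, before sternotomy) and the first shunt reading (before surgery) come earlier and cannot carry a CPAP effect. The two randomizations are independent. Adjustment is valid here.
- *PEEP factor.* The Interventions section places the test after induction, and the Endpoints section places it before or after sternotomy. The EFL determination section describes the test as a 3 cmH2O reduction of PEEP. The Lung mechanics section reads mechanics right after the test. None of them says which PEEP is in use at the first reading or whether it is common to all arms. Validity cannot be settled from the text.

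**5. Shunt schedule.** Trial design implies five determinations. Shunt fraction calculation and Table 4 give two. With two, there is one later value, so analysis of covariance is enough and no repeated-measures model is needed.

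**The case against.** The strongest reply is that the sentence is short because the article is short. Analysis of variance may include factorial or repeated-measures forms, the detail may lie in the plan not shown, and the variables are not endpoints. Much of this stands. The article does not say one-way, does not say each stage is tested alone and does not say the first reading is discarded. A reader might infer all three from the pairing with Kruskal-Wallis, but that remains an inference. What survives is narrower: the article does state a rule for every continuous variable, and one of its two options cannot use the structure of these data.

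A reader might also infer heavy multiple testing: three mechanics variables × five rows × two factors = 30 tests, with 1 − 0.95³⁰ = 79% chance of a false positive. The documents do not support that figure. It counts the first reading as an outcome, treats correlated readings as independent, and assumes a stage-by-stage plan that is not stated. Table 4 has only one compliance column, and shunt has one later reading.

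Finally, if the first reading were already at the allocated PEEP, adjusting for it could remove part of the PEEP effect. This is a fair limit on the remedy. The text leaves the order unclear; it does not show that the reading is affected. The CPAP factor is untouched by it.

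**Conclusion.** The point holds as a minor improvement. Compliance, airway resistance and shunt have repeated readings, and the stated method names no way to use them. The likely loss is an interval 5% to 29% narrower forgone for r between 0.3 and 0.7. That range rests on assumed correlations. The chest is opened between first and later readings, so a high correlation should not be taken for granted.

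The gain is available now for the CPAP factor. For the PEEP factor it depends on the order of the first reading and the allocated PEEP. A larger gain from pooling all later readings should not be claimed: it needs an effect constant over stages, and the after-sternotomy reading precedes CPB, so it cannot show a CPAP effect.

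A reader might take the point to weaken the main result. It does not. The primary composite is binary. Among the listed secondary endpoints, the stated rule suits durations and lengths of stay, which have no first reading. The sample size is unchanged.

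**What to change.** 1. **Data analysis.** Limit the present sentence to continuous variables measured once, and keep rank methods for durations and lengths of stay. Add for the repeated measures:
   - Each mechanics measure is analysed in one linear mixed model of the later readings (log scale if skewed), linking readings within patient, with PEEP, CPAP, stage and the factor-by-stage terms, and with the first reading as covariate.
   - End-of-surgery shunt is analysed by analysis of covariance on the first value, with both factors.
   - The first reading serves as covariate for the PEEP factor only if it precedes the allocated PEEP. Otherwise the PEEP effect is taken from the same model without it, and the CPAP effect from the model with it.
2. **Interventions, EFL determination and Lung mechanics determination.** Reconcile these sections, together with the timing of the test under Endpoints, so that the article says whether the first reading precedes the allocated PEEP.
3. **Trial design against Shunt fraction calculation and Table 4.** Reconcile five shunt time-points with two.

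The cost is a few sentences and slightly more modelling work, with no added patients or measurements. Item 2 is best settled before recruitment, because an inconsistent first reading cannot be repaired at analysis.

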### Endpoints

The primary endpoint will be a composite endpoint of the incidence of EFL after CPB and of PPCs at 5 days after surgery (see Table 2 for complete definition of PPCs). Before/after sternotomy, a PEEP test will provide the best PEEP value, that will be the least value of PEEP for which closing capacity does not exceed the FRC, leading to the avoidance of EFL and atelectasis. In practice, the EFL phenomenon will be assessed at different PEEP levels, until the abrupt decrease in end-expiratory pressure will cause an increment in expiratory flow. At this level the patient will not be flow-limited and this will be considerate his best PEEP for the rest of surgery.

**Table 2 Tab2:** Definition of postoperative pulmonary complications (PPCs), Jammer et al*.* [24]

Complication	Definition
Respiratory infection	Patient has received antibiotics for a suspected respiratory infection and met one or more of the following criteria: new or changed sputum, new or changed lung opacities, fever, white blood cell count > 12 × 10^9^ l^-1^
Respiratory failure	Postoperative PaO_2_ < 8 kPa (60 mmHg) on room air, a PaO_2_:FIO_2_ ratio < 40 kPa (300 mmHg) or arterial oxyhemoglobin saturation measured with pulse oximetry < 90% and requiring oxygen therapy
Pleural effusion	Chest radiograph demonstrating blunting of the costophrenic angle, loss of sharp silhouette of the ipsilateral hemidiaphragm in upright position, evidence of displacement of adjacent anatomical structures or (in supine position) a hazy opacity in one hemithorax with preserved vascular shadows
Atelectasis	Lung opacification with a shift of the mediastinum, hilum, or hemidiaphragm toward the affected area, and compensatory over-inflation in the adjacent non-atelectatic lung
Pneumothorax	Air in the pleural space with no vascular bed surrounding the visceral pleura
Bronchospasm	Newly detected expiratory wheezing treated with bronchodilators
Aspiration pneumonitis	Acute lung injury after the inhalation of regurgitated gastric contents

*PaO*_*2*_ arterial partial oxygen pressure, *FiO*_*2*_ fraction of inspired oxygen

The secondary endpoints will be the evaluation of the following:Readmission to the intensive care unit (ICU)Need for re-intubationNeed for non-invasive ventilationDuration of mechanical ventilationPostoperative infectionsMajor adverse cardiac events (MACE; see Table 3 for complete definition of MACE)Length of the ICU and hospital stay30-day and 1-year mortality

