### Postoperative ventilation

Mechanical ventilation setting used during patient transfer from the operating theater to the ICU will be reported in appropriate case report form (CRF). In the ICU it will be applied a volume-controlled continuous mandatory ventilation (VC-CMV) with the same parameters used in the operating room. Blood oxygen saturation will be constantly monitored with a pulse oximeter; blood-gas analyses will be performed according to clinical needs.

Following data will be collected: extubation time, duration of mechanical ventilation and need for re-intubation.

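### A Hodges-Lehmann estimate is labelled a difference between medians, which it equals only under a pure shift or certain symmetric shapes

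*Protocol article*

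**What the plan says.** Under Data analysis, the protocol article gives two statements for continuous outcomes. On testing: "Continuous variables will be compared by analysis of variance or the non-parametric Kruskal-Wallis test". On estimation: "differences between medians with 95% confidence intervals (using the Hodges-Lehmann estimation) will be calculated when appropriate". No variable is tied to either statement, and no location-shift assumption is made.

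The listed outcomes to which a median difference would most naturally apply are secondary. Endpoints includes ventilation time and "Length of the ICU and hospital stay", and Postoperative ventilation lists "duration of mechanical ventilation" among the data collected. The document gives no distribution and no expected effect for any of them.

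The primary endpoint is binary: "The primary endpoint will be a composite endpoint of the incidence of EFL after CPB and of PPCs at 5 days after surgery". It falls under the chi-square test and relative risks.

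**The concern.** The sentence names one quantity and a method for another. The difference between medians compares the middle of one group with the middle of the other. Hodges-Lehmann takes every between-group pair, forms the difference, and reports the median of those differences. Its interval inverts a rank test under a shift model.

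Durations after cardiac surgery are plausibly right-skewed. A strategy that prevents complications in some patients would change the upper part of the distribution and would not move every patient by the same amount. The published table could then show two medians beside a stated difference between medians that does not equal their difference. Its interval would not necessarily have 95% coverage for that difference. At stake is the correct reading of secondary effect sizes, not the trial's main conclusion.

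**Working it through.** **Group size.** The Sample size section states "we anticipate that the 50% of patients with ventilation cessation during CPB and no PEEP before and after CPB" and "only the 30% of the patients treated with an optimal ventilatory strategy will develop this composite endpoint". With two-sided 0.05, 80% power and unpooled variance:

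n = (1.960 + 0.842)² × (0.5×0.5 + 0.3×0.7) / 0.2² = 7.85 × 0.46 / 0.04 = 90.3, so 91.

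91 / 0.9 = 101.1, so 102 per side and 204 in total, which is the plan's figure (four cells of 51). Each factor's margin therefore compares 102 with 102.

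**The two quantities differ.** An invented example: group A = 7, 8, 20 and group B = 5, 8, 9. Both medians are 8, so the difference between medians is 0. The nine differences A − B, sorted, are −2, −1, −1, 0, 2, 3, 11, 12, 15. Their median, the Hodges-Lehmann estimate, is 2.

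**The interval.** Sort the m×n pairwise differences and take k = floor(mn/2 − 1.96·√(mn(m+n+1)/12)). With m = n = 102, mn = 10,404 and k = floor(5,202 − 1.96×421.6) = 4,375. The interval runs from the 4,375th to the 6,030th ordered difference.

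**Coverage by simulation**, 102 v 102, mostly 2,000 simulated trials per row. All shapes are assumptions. Differences are shown as absolute values, in hours unless days are stated.

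| Assumed shape | True median difference | Hodges-Lehmann target | Coverage of median difference | Coverage of Hodges-Lehmann target |
|---|---|---|---|---|
| No effect (lognormal, median 12 h, log-SD 0.8) | 0 | 0 | 94.6% | 94.6% |
| Pure shift of 2 h | 2.0 | 2.0 | 94.8% | 94.8% |
| Ratio 1.25, log-SD 0.5 | 3.0 | 2.8 | 94.8% | 95.3% |
| Ratio 1.25, log-SD 0.8 | 3.0 | 2.6 | about 93% | 94–95% |
| Ratio 1.5, log-SD 0.8 | 6.0 | 5.2 | 92% | 95% |
| Ratio 1.5, log-SD 1.0 | 6.0 | 4.8 | 90% | 94% |
| Ratio 2, log-SD 0.8 | 12.0 | 10.6 | 89% | 94% |
| Long tail in 30% v 15% (10 h; tail 60 h) | 1.6 | 1.7 | 94–95% | 94–95% |
| Long tail in 50% v 30% (10 h; tail 60 h) | 8.0 | 3.9 | 63–67% | 95% |
| Long tail in 50% v 30% (8 h; tail 24, 36 or 48 h) | 2.1, 3.4, 4.6 | 1.7, 2.4, 2.8 | 93%, 86%, 78% | 94–95% |
| Hospital stay in whole days, ratio 1.3 | 3 days | 2 days | 86% | 99.7% |
| ICU stay in whole days, tail 30% v 15% | 1 day | 0 days | 44% | 100% |

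With 51 v 51 (single cells), coverage of the median difference was 92–96% in the shapes run, except 77% for the 50% v 30% tail of 60 h and 67% for the rounded ICU days.

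**Equal medians, shorter upper tail.** With both medians at 8 h and upper log-SD 0.6 v 0.9, 0.4 v 0.8, 0.5 v 1.0 and 0.4 v 1.2, the interval excludes zero in about 12%, 24–26%, 26% and 44% of trials. When the log-scale spread differs symmetrically instead (0.8 v 0.5; 1.2 v 0.5), coverage of zero is 95.1% and 92.9%.

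**The case against.** Hodges-Lehmann is the usual companion to a rank test, and it is valid for its own quantity in every continuous shape tried (93–96%). The article says it applies only when appropriate, names no variable, and refers to a pre-established analysis plan that is not shown. All of that is fair and keeps the point small. It does not make the named quantity match the named method, and that mismatch is in the article itself.

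A reader might infer three stronger things. The documents support none of them.

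- *That these intervals will generally cover well under 95%.* The large shortfalls need particular shapes: about half the patients in a long tail, whole-day rounding where the median jumps, or a shortened upper half with medians held equal. The article neither states nor rules these out.
- *That the planned 50% and 30% supply such a shape.* Those are rates of a composite that includes EFL detected in the operating room, and nothing says EFL alone prolongs ventilation. The Background cites pulmonary complication rates of 3–16% after bypass grafting and 5–7% after valve surgery. With long ventilation in 16% v 8%, coverage is 94.5–95.3%. This high-risk cohort and the broad definitions in Table 2 could give more complications, so the matter is open. The 50% and 30% are also worded as a contrast between extreme strategies. If each factor contributed half (an assumption), a margin would be 45% v 35%, with coverage of 94.6%, 92.7% and 92.0% for tails of 24, 36 and 48 h.
- *That excluding zero in 12–44% of trials with equal medians is an inflated false-positive rate.* In those scenarios one group's upper tail really is shorter. The interval detects a real distributional difference, as the planned rank test would. It is wrong only when read as a statement about medians.

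**Conclusion.** The point holds as a minor labelling error: the quantity named under Data analysis is not the one Hodges-Lehmann estimates. Its size cannot be fixed from the document. In the assumed shapes, coverage of the true median difference is close to nominal with no effect or a longer tail in a minority. It is 90–92% for a lognormal ratio of 1.5 and about 93% for 1.25 (log-SD 0.8), and 89% for a doubling. Only special shapes take it far lower.

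The discrepancy in the estimate itself can be visible in a table, for example 5.2 h against a 6.0 h difference between medians at a ratio of 1.5. The primary composite, the 204 patients and all planned p-values stand.

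**What to change.** Under Data analysis, keep the method and rename the quantity: *Hodges-Lehmann location shift (median of all pairwise between-group differences) with 95% confidence interval*. Do not present it as the difference between the two medians. This costs one phrase and no patients, data or power. The article says recruitment has not started, so it can be settled before any results are seen.

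Only if a difference between medians is specifically wanted, replace the method with a bootstrap or quantile-regression interval. The percentile bootstrap covered about 95–97% in the continuous shapes and 92–99.7% on whole-day data. The price is precision: its interval was about 25% to 115% wider than the Hodges-Lehmann interval in the shapes compared.
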